# Efficacy of the unified protocol for the treatment of emotional disorders in the Spanish public mental health system using a group format: study protocol for a multicenter, randomized, non-inferiority controlled trial

**DOI:** 10.1186/s12955-018-0866-2

**Published:** 2018-03-12

**Keywords:** Unified protocol, Transdiagnostic, Emotional disorders, Group therapy, Public mental health, Multicenter, Randomized, Controlled trial

## Abstract

**Background:**

Emotional disorders, which include both anxiety and depressive disorders, are the most prevalent psychological disorders according to recent epidemiological studies. Consequently, public costs associated with their treatment have become a matter of concern for public health systems, which face long waiting lists. Because of their high prevalence in the population, finding an effective treatment for emotional disorders has become a key goal of today’s clinical psychology. The Unified Protocol for the Transdiagnostic Treatment of Emotional Disorders might serve the aforementioned purpose, as it can be applied to a variety of disorders simultaneously and it can be easily performed in a group format.

**Methods:**

The study is a multicenter, randomized, non-inferiority controlled clinical trial. Participants will be 220 individuals with emotional disorders, who are randomized to either a treatment as usual (individual cognitive behavioral therapy) or to a Unified Protocol condition in group format. Depression, anxiety, and diagnostic criteria are the primary outcome measures. Secondary measures include the assessment of positive and negative affect, anxiety control, personality traits, overall adjustment, and quality of life. An analysis of treatment satisfaction is also conducted. Assessment points include baseline, post-treatment, and three follow-ups at 3, 6, and 12 months. To control for missing data and possible biases, intention-to-treat and per-protocol analyses will be performed.

**Discussion:**

This is the first randomized, controlled clinical trial to test the effectiveness of a transdiagnostic intervention in a group format for the treatment of emotional disorders in public settings in Spain. Results obtained from this study may have important clinical, social, and economic implications for public mental health settings in Spain.

**Trial registration:**

Retrospectively registered at https://clinicaltrials.gov/. Trial NCT03064477 (March 10, 2017). The trial is active and recruitment is ongoing. Recruitment is expected to finish by January 2020.

## Background

Emotional disorders (EDs; i.e., depressive and anxiety disorders) have become the most prevalent psychiatric disorders globally [1]. The 12-month prevalence of anxiety and depressive disorders affect 14% and 7.8% (6.9% by major depression) of the population, respectively [2], and comordibity may be as high as 50% [3]. Lifetime prevalence rates in primary care settings in Spain reveal that mood and anxiety disorders, as defined in the DSM-IV-TR) [4], are the most prevalent psychiatric problems as well, with 35.8% and 25.6%, respectively [5].

As a result of their high prevalence in the population, EDs have become a global health problem due to their associated costs. For instance, a study conducted in 36 countries estimated that the annual treatment cost of depressive disorders and anxiety problems amounted to $91 billion and $56 billion, respectively [6]. It has been calculated that more than 12 billion days of productivity loss are attributable to depression and anxiety disorders every year, which results in $925 billion in productivity losses. In Spain, when direct and indirect costs are included, mood and anxiety disorders (again, according to DMS-IV-TR categories), are estimated to cost approximately $10.76 billion and $10.36 billion, respectively [7]. The high prevalence and important burden of EDs indicate that there is an urgent need to enhance the effectiveness of treatments for EDs in public mental health systems.

The Unified Protocol (UP) for the Treatment of Emotional Disorders [8, 9] is a recently developed form of cognitive behavioral therapy (CBT).The UP can be applied to a variety of disorders simultaneously and it can be easily performed in a group format. The UP was created on the basis of the identification of common psychopathological vulnerability factors in EDs [1, 10].In the UP, traditional CBT techniques (i.e., cognitive restructuring) are combined with more novel psychological skills (i.e., increasing awareness) to treat emotion regulation deficits, which are argued to be the underlying common factors in all EDs [11]. The UP is a structured, manual-based treatment [8, 9] which facilitates group delivery when patients present different EDs [11]. This, together with the fact that the UP can be applied simultaneously to individuals with different EDs, might help reduce existent waiting lists and current costs of individual treatment.

So far, studies exploring the effectiveness of the UP in a group format have led to promising findings [12–15].Overall, results suggest that the UP obtains medium-to-large effect sizes on numerous outcomes, including depression, anxiety, positive and negative affect, quality of life, overall adjustment, and avoidance of negative sensations, for both anxiety and mood disorders [12–14]. These studies have also revealed that between half and two thirds of patients ceased to meet diagnostic criteria after the treatment and one investigation, conducted by our team, revealed that changes remained stable 12 months after treatment completion [13]. Despite the previous results are encouraging, conclusions should be interpreted with caution as sample sizes have been small (11 participants in two studies and 47 patients in one investigation). Methodologically-sound, randomized, controlled trials are needed in order to replicate the aforementioned findings and to elucidate whether the UP in group format is indeed an effective treatment option for EDs in public settings.

The present non-inferiority, randomized, controlled trial will compare the efficacy of the UP in group format against traditional individual CBT treatment in a sample of patients with EDs. Ultimately, our goal is to explore whether the UP in group format can be an effective psychological intervention for EDs in the Spanish National Health System, that is, one that generates long-lasting changes in symptoms. To ensure the generalizability of results, our goal is tested in various public mental health centers in Spain.

## Methods/design

The current study is a non-inferiority, multicenter, randomized, controlled clinical trial with two treatment groups: UP in group format and traditional CBT in individual format (treatment as usual, TAU). A conservative, non-inferiority design was selected because, to the best of our knowledge, this is the first randomized controlled trial to compare the UP in a group format against individual CBT in public mental health settings.

In the present investigation, all consecutive patients with EDs attending any of the collaborating centers (see “Sample and recruitment” section) are asked to participate. Once inclusion criteria are met (see “Inclusion and exclusion criteria” section), each patient is randomly assigned to one of the two experimental groups: TAU or UP (see “Procedure” section). The study includes 5 assessment points (baseline, post-treatment, and three follow-ups at 3, 6, and 12 months after treatment completion). The flow chart of study design is shown in Fig. 1. Also, a schedule of enrolment, interventions, and assessments is reported following the Standard Protocol Items: Recommendations for Interventional Trials (SPIRIT) guidelines (Fig. 2). Note that, despite treatment occurs at different frequencies between conditions (approximately once a month in the TAU condition and weekly in the UP group), assessment points are the same for both groups.

**Fig. 1 Fig1:**
[figure not shown]
Study flow chart

**Fig. 2 Fig2:**
[figure not shown]
Study schedule of enrolment, interventions, and assessments

### Sample and recruitment

The trial started the recruitment in September 2014 and it is still active. The study is conducted in five different Public Mental Health Centers and Primary Care Centers in Spain, namely, the Elda Clinical General Hospital, the Hospital Clínico Universitario de Valencia, the [name] Hospital, the PCC IIA Milagrosa of Pamplona, and the Hospital Comarcal de Vinaròs. Participants are individuals over 18 years of age seeking psychological assistance in the Spanish Public Health System. Sample size was set to 220 participants to ensure enough statistical power when testing our hypotheses (see “Sample size” section).

Patients are referred to the study by licensed psychologists, psychiatrists, and clinical psychology residents working at the collaborating centers, who also assess for current DSM diagnoses (See “measures” section) and the remaining eligibility criteria (see “Inclusion and exclusion criteria” section). Individuals with comorbid diagnosis of several EDs are also enrolled in the study. The existence of such comorbidities might be important for assessment scores. However, in the present study we did not stratify considering comorbidities because this could significantly increase the complexity of the design (i.e., some patients might have more than one comorbid diagnosis). Due to the difficulties derived from conducting an RCT in different public mental health settings, we cannot guarantee a 100% of independent evaluations. We expect between 60 to 75% of independent evaluations. The rest of evaluations will probably be made by recruiters who are also the therapists in one of the conditions. However, this information is collected and considered in the interpretation of results.

Patients meeting eligibility criteria are asked to participate and are provided with an information sheet, information on data confidentiality, and an informed consent form. After participation acceptance, patients complete the baseline assessment protocol in their correspondent health center (see “Measures” section). Next, participants are informed of the condition they have been randomly assigned to, that is, TAU or UP.

Enrollment period and waiting time are comparable across participants (2–3 weeks). When the time from assessment, diagnosis, and randomization to the onset of the intervention takes more than 2 weeks we establish a new period of assessment. For ethical reasons, if a patient feels uncomfortable with the group format at any time during the study, he/she is allowed to join the TAU condition. This information is collected and considered in the analyses.

### Sample size

To calculate the sample size required, the non-inferiority margin (i.e., tolerable amount of effect difference between TAU and the UP) has to be set. This was done according to the US Food and Drug Administration (FAD) [16] guidelines. First, the effect of the active control (i.e., CBT) compared with placebo needs to be established, based on previous research. Meta-analyses indicate medium-to-large effect sizes (between .4 and .8) of individual CBT on EDs [17–19]. Then, an amount of minimum preserved effect needs to be set. According to FDA guidelines, a preserved effect of a 50% of the effect of the active control (individual CBT) is recommended, so this was set to .3 in the present study. Because, to the best of our knowledge, no meta-analysis has reported effect sizes for each outcome included in the study, the margin has been defined according to the pooled estimate of overall effectiveness of CBT.

With regards to treatment satisfaction, a 35% non-inferiority margin was established. This is based on a meta-analysis of computer CBT, in which between 70% and 100% of depressed patients were satisfied with treatment [20]. To the best of our knowledge, there is no meta-analysis of treatment satisfaction with individual, face-to-face CBT and its study is rare. However, similar to group UP, computer CBT has been argued to be an alternative to traditional CBT [20], especially when resources are limited, so the aforementioned satisfaction rates of computer CBT might be relevant in the present study.

We obtained a sample size of 95 participants for each group with 80% power, an alpha level of .05 (one-sided), a standard deviation of .83 in the CBT group compared with placebo, and a non-inferiority limit of .30 [21, 22]. Considering a drop-out of 15%, we decided to recruit 110 subjects in each group. When registering the study, a sample size of 200 individuals was calculated. However, this was increased by 20 patients after considering non-inferiority sample size calculations.

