To address problems of missing data or premature dropouts, an intention-to-treat analysis will be used and the most recent data will be imputed (last observation carried forward approach). This analytic strategy will only be performed with patients attending at least 50% of sessions, as recommended in past research [41], and with those responding to at least one of the post-treatment assessments (i.e., end of treatment or follow-ups) so that treatment effect may be captured by the last observation. In addition to the last observation forward, missing data in the UP group will also be replaced with the CBT mean +/− the non-inferiority margin and missing data in the CBT group will be replaced with the UP mean (i.e., bias toward inferiority) [42]. Results using a last observation carried forward approach and a bias toward inferiority imputation will be compared against a completers-only strategy and all of them will be reported. To ensure non-inferiority, a per-protocol analysis will also be conducted. Following FDA guidelines [16], non-inferiority will be concluded if the upper bound of the 95% CI for the effect estimate in the UP condition is smaller than the non-inferiority margin (50% of the effect estimate of individual CBT when compared to placebo). Due to the non-inferiority design (i.e., the Unified Protocol in a group format is not worse than individual CBT), a one-sided confidence interval will be used in the analyses. A post-hoc power analysis with the primary outcomes will be conducted at post-treatment and follow-ups using the sample size and obtained effect size.

The researcher analyzing data, [name], will be blind to arm allocation. To ensure that, arms will be given arbitrary letters (A and B) in the database and only the lead researcher, [name], will know the correspondence between study allocation arms and assigned arbitrary letters.

Reporting of results will follow the Consolidated Standards of Reporting Trials (CONSORT) recommendations [43].

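### The .30 margin preserves half of the CBT effect only if that effect is at least .60, a value the protocol does not state, and the 35% satisfaction margin appears to be half of a raw satisfaction rate.

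*Protocol article*

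**What the plan says.** All of the margin reasoning is in the Sample size section of the protocol article. It starts from the size of the control effect: "Meta-analyses indicate medium-to-large effect sizes (between .4 and .8) of individual CBT on EDs". It then sets the margin: "a preserved effect of a 50% of the effect of the active control (individual CBT) is recommended, so this was set to .3". It adds that, for want of outcome-specific meta-analyses, "the margin has been defined according to the pooled estimate of overall effectiveness of CBT". The value of that pooled estimate and its uncertainty are not given.

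The Analyses section carries the 50% property into the decision rule. Non-inferiority is concluded when the upper confidence bound lies under "the non-inferiority margin (50% of the effect estimate of individual CBT when compared to placebo"), and no number is repeated there.

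For satisfaction, the Sample size section says "a 35% non-inferiority margin was established". The basis is a meta-analysis of computer CBT in which "between 70% and 100% of depressed patients were satisfied with treatment". The section acknowledges that it found no meta-analysis of satisfaction with individual face-to-face CBT. It does not say whether 35% means absolute points or a relative reduction.

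**The concern.** A preserved fraction depends on the control effect from which it is taken. The protocol cites a range whose upper end is twice its lower end, names one margin, and attaches one preservation figure to it without a condition. Over the lower half of that range the figure is not met. Because the decision rule describes the margin as half of the CBT effect, a reader of a positive result would take it that at least half of the benefit of CBT is retained. The cited figures support that only if the CBT effect is at least .60.

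The satisfaction margin has a different weakness. The only evident way to reach 35 is to halve 70, the lower of the two cited rates. That is a raw proportion from another treatment with no comparator rate subtracted, so it does not follow the logic used for efficacy. It is also wide enough that a clear loss of satisfaction could be reported as non-inferior.

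**Working it through.** **Inputs from the Sample size section:** CBT effect .4 to .8; margin .30; SD .83; one-sided alpha .05; 80% power; 95 per arm; satisfaction margin 35%; computer-CBT satisfaction 70% to 100%.

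**1. The plan's own sample size.** n per arm = 2 × (1.645 + 0.842)² × .83² / .30² = 94.7, rounded up to 95. This matches "We obtained a sample size of 95 participants for each group with 80% power", so the sample size is not in error on its stated inputs.

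**2. Share of the CBT effect preserved at the margin** = 1 − .30/effect.

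| CBT effect | Preserved | Half of the effect |
|---|---|---|
| .4 | 25% | .20 |
| .5 | 40% | .25 |
| .6 | 50% | .30 |
| .8 | 62.5% | .40 |

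Over the cited range, half of the effect is anything from .20 to .40. It equals .30 at one point only.

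**3. What a pass at .30 requires.** The half-width of the one-sided bound is 1.645 × .83 × √(2/95) = .198. UP passes if its observed deficit is below .30 − .198 = .102. If the true deficit were exactly .30, it would pass 5% of the time.

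**4. What a reading at .20 would require.** The observed deficit must be below .20 − .198 = .002, so UP must look about as good as TAU or better. If the treatments are truly equal, the chance of this with 95 per arm is Φ(.20/(.83 × √(2/95)) − 1.645) = Φ(.016) = 51%. With SD 1 it is Φ(−.267) = 39%. At 80% power and SD .83, a margin of .20 would need 213 per arm.

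A caveat on scale: step 2 treats .30 as being on the same scale as the cited effect sizes, while steps 1, 3 and 4 use the plan's SD of .83. If .30 is a standardized difference, the SD would be 1, which is why both values are shown in step 4.

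**5. Satisfaction.** Assumptions, none stated in the protocol: a binary satisfied/not satisfied endpoint, 35% as absolute points, a one-sided 5% bound, 95 per arm, and 70% satisfied on TAU.

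- 47% on UP: SE = √((.70 × .30 + .47 × .53)/95) = .0695; upper bound = .23 + 1.645 × .0695 = .344, below .35, so it passes.
- 46% on UP: upper bound = .24 + 1.645 × .0695 = .354, so it fails.
- True rate of 50% on UP: SE = √((.21 + .25)/95) = .0696; chance of passing = Φ((.35 − .20)/.0696 − 1.645) = Φ(.51), about 70%.
- True rate of 55% on UP: SE = √((.21 + .2475)/95) = .0694; chance of passing = Φ((.35 − .15)/.0694 − 1.645) = Φ(1.24), about 89%.

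The lowest rate the margin tolerates depends on the reading. In absolute points, 70% falls to 35% and 100% falls to 65%. As a relative reduction, 70% falls to 70% × .65 = 45.5%.

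**The case against.** The strongest reply on efficacy is that the protocol ties the margin to a pooled estimate, not to the lower end of a range. At the implied .60 exactly half is preserved, and above it more. The span .4 to .8 is not presented as a confidence interval, and nothing in the document obliges the authors to use its lowest value. This stands, and it rules out saying that the margin simply fails to do what is claimed. It does not remove the point that the pooled value must be at least .60 for the claim to hold. A fuller protocol may give that value, but the article prints only the range, and half of that range does not support an unconditional 50%.

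A reader might infer that a positive trial would leave UP with a quarter of the benefit of CBT. The decision rule does not support that. A pass needs an observed deficit below about .10, which is 75% of the effect kept even if that effect is .4. The 25% is the boundary that a pass fails to exclude by more than a hair, not a likely outcome.

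A reader might also argue that TAU, roughly monthly and unstandardised, must sit at the low end of the range. The document gives no figure for this. TAU also comes with medication and continues until clinician and patient agree that it has worked, which could push the other way.

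On satisfaction, the protocol claims no preserved fraction, so it cannot be said to break one. It is open about borrowing from computer CBT, and satisfaction is not among its primary outcomes. Satisfaction could halve at the margin only from 70% and only in absolute points. To say that the test can hardly fail is too strong, since one point lower than the 47% example already fails. With a two-sided 95% interval the 47% example itself fails, at .23 + 1.96 × .0695 = 36.6 points. The Treatment Opinion Scale uses 4-point and 11-point items with no stated cut-off, so the binary calculation is illustrative.

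**Conclusion.** The point holds in a limited form. The 50% preservation attached to .30 is conditional on a CBT effect of at least .60, and the protocol presents it without that condition. Below .60 the share falls to 40% at .5 and 25% at .4; above it the share rises to 62.5% at .8. This rests only on the protocol's own range and on reading .30 on the same scale as that range. It does not show that .30 is wrong or that 95 per arm is too few on the stated inputs.

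The satisfaction margin is weakly founded: it appears to be half of a raw rate from a different treatment. Under the assumptions listed it would pass a true 20-point deficit about 70% of the time. That size depends on the absolute, binary reading. The wider conclusion, that neither margin preserves what is claimed, is not supported: the efficacy margin does so at .60 and above, and no such claim is made for satisfaction.

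**What to change.** Keep the margin of .30 and the sample size. In the Sample size section, state the pooled CBT effect behind .30 and say that half of it is preserved only if it is at least .60, with 25% preserved at .40. In the Analyses section, limit the primary conclusion to non-inferiority within .30. Report the upper bound against .20 as a descriptive sensitivity reading, and make no claim that at least half of the CBT effect is preserved over the cited range without that reading. It should stay descriptive: as a formal second criterion it would have only 39% to 51% power even if the treatments are equal, and whether that is worth having is debatable.

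Drop the 35% non-inferiority claim and report the satisfaction difference with its confidence interval.

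Recruitment was still open when the article appeared, so this can be settled before analysis and needs no extra patients. The cost is a more modest primary claim and the loss of a pre-specified satisfaction criterion, which becomes descriptive.

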### Secondary outcomes

We administer the Overall Depression Severity and Impairment Scale (ODSIS) [30] and the Overall Anxiety Severity and Impairment Scale (OASIS) [31] weekly to assess the severity of depressive and anxiety symptoms, respectively. These measures are included to complement the results obtained with the BDI-II and the BAI, as well as to obtain a continuous assessment. The Positive and Negative Affect Scale (PANAS) [32, 33] is administered to evaluate positive and negative affect. The perception of control over anxiety is assessed by means of the Anxiety Control Questionnaire-Revised (ACQ-R) [34, 35]. Personality is measured with the NEO Five-Factor Inventory (NEO-FFI) [36], which offers a rapid and general measure of the Big Five personality traits: Neuroticism, Extraversion, Openness to experience, Agreeableness, and Conscientiousness. The Quality of Life Index (QLI) [37] is used to evaluate several aspects of health-related quality of life (i.e., physical disability, emotional well-being, self-care and independent functioning, occupational functioning, interpersonal functioning, social emotional support, community and services support, personal fulfillment, spiritual fulfillment, and overall quality of life). Similarly, the Maladjustment Inventory (MI) [38] is used to evaluate the extent to which the subject’s current problems impact negatively on different areas of daily life, namely, work, social life, leisure time, relationship with the partner, family life, and overall adjustment in daily activities. Additionally, we created an ad hoc questionnaire, the Treatment Opinion Scale (OTS), which is administered to participants in both conditions. Our ad hoc questionnaire evaluates the quality of the intervention (i.e., “How would you rate the quality of the treatment program you have received?”) and that of its components (i.e., “Have the techniques and exercises that we have practiced helped you regulate your emotions properly?”). Also, it measures the amount of discomfort experienced during treatment (i.e., “To what extent has this treatment caused you discomfort?”) and the experience of participating in a group format (i.e., “If you were to seek help again, would you choose a group treatment program?”). Some questions in the OTS use a4-point Likert scale (0 = “*poor”* or “*nothing”* to 3 = “*excellent”* or “*very much”*), while an 11-point response scale is selected in some items (0 = “*nothing”* to 10 = “*very much”*).

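### One .30 margin, taken from the pooled CBT effect, also governs non-symptom secondary scales for which the protocol gives no CBT effect, so a pass on those scales need not show any preserved benefit

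*Protocol article*

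**What the plan says.** Under Sample size, the protocol builds the margin in steps. It starts from the effect of individual CBT over placebo: "Meta-analyses indicate medium-to-large effect sizes (between .4 and .8) of individual CBT on EDs". It then preserves 50% of that effect and sets the margin at .3. It explains the single figure by saying that "no meta-analysis has reported effect sizes for each outcome included in the study, the margin has been defined according to the pooled estimate of overall" (CBT benefit in general). The calculation that follows uses "a standard deviation of .83 in the CBT group compared with placebo, and a non-inferiority limit of .30". Treatment satisfaction is treated separately, with a margin of 35% from its own source.

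Under Analyses, the rule is that "non-inferiority will be concluded if the upper bound of the 95% CI for the effect estimate in the UP condition is smaller than the non-inferiority" limit, which is described there as 50% of the CBT effect over placebo. No outcomes are named. The post-hoc power analysis in the same paragraph, by contrast, is expressly confined to the primary outcomes.

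Under Secondary outcomes, the continuous scales are ODSIS, OASIS, PANAS, ACQ-R, NEO-FFI, QLI and MI. The NEO-FFI is included as an instrument "which offers a rapid and general measure of the Big Five personality traits: Neuroticism, Extraversion, Openness to experience, Agreeableness, and Conscientiousness".

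**The concern.** A preserved-effect margin has meaning only in relation to the control's effect on the outcome being tested. The pooled range of .4 to .8 is the effect of CBT on emotional disorders, which fits symptom scales. The protocol cites no CBT-versus-placebo effect on affect, perceived anxiety control, personality, quality of life or maladjustment. It acknowledges that effects for each outcome are not available and uses the pooled figure instead.

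If CBT moves a scale by .30 or less, being within .30 of CBT includes doing nothing at all. A pass on that scale could be reported as non-inferiority to individual CBT and read as support for the UP, when it shows only that the two arms differ little on a scale that CBT hardly moves. The NEO-FFI traits are the plausible case. The Background lists UP effects on affect, quality of life and adjustment, but on no personality trait.

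**Working it through.** **Inputs.** From Sample size: margin .30, SD .83, 95 per arm, 80% power, one-sided alpha .05, and a CBT effect of .4 to .8. The CBT effect d on each secondary scale is not given, so it is an assumption and is shown as a range.

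**Step 1: reproduce the plan's figure.** With no true difference, n per arm = 2 × (z.95 + z.80)² × SD² / margin² = 2 × (1.645 + 0.842)² × .83² / .30² = 94.7, rounded up to 95. This matches the stated 95.

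**Step 2: what the margin concedes.** The share of the CBT effect that may be lost is .30/d.
- d = .4: 75%
- d = .6: 50%
- d = .8: 37.5%
- d = .3 or less: 100% or more

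The 50% logic is therefore met only at d of about .60, the midpoint of the quoted range.

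**Step 3: chance that a UP with no effect on the scale is declared non-inferior.** If the UP effect is zero, the true shortfall against CBT is d. Then

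P(pass) = Φ((.30 − d)/SE − 1.645), with SE = .83 × √(2/95) = .1204.

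| Assumed CBT effect d | (.30 − d)/SE − 1.645 | P(pass) |
|---|---|---|
| 0 | 0.85 | 80% |
| .10 | 0.02 | 51% |
| .20 | −0.81 | 21% |
| .30 | −1.645 | 5% |
| .40 | −2.48 | 0.7% |
| .60 | −4.14 | <0.1% |

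The chance is above one half only if d is below .30 − 1.645 × .1204 = .10.

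**Step 4: sensitivity.**
- SD 1 with 95 per arm: SE = .1451. P(pass) is 66% at d = 0 and 40% at d = .10. The 50% point is .30 − 1.645 × .1451 = .06.
- 110 analysed per arm, SD .83: 85% at d = 0.
- Two-sided 95% interval, 95 per arm, SD .83: 70% at d = 0.
- Assumed ICC of .05 in UP groups of 9, SD .83: about 74% at d = 0.

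**Step 5: outcome-specific margins for comparison.** With a margin of d/2, SD .83 and 95 per arm, a UP with no effect passes in at most 2% of trials for d from .1 to .8. For 80% power, n per arm would be 3,408 at d = .1, 852 at .2, 379 at .3 and 213 at .4. Where CBT has a small effect, this trial therefore could not support a properly scaled non-inferiority claim.

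**The case against.** Several objections have force.

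- **Scope.** A reader might infer that .30 is applied to every outcome. The protocol does not support that. Satisfaction has its own 35% margin, and diagnostic status, a primary outcome, is categorical, so a standardized mean margin does not obviously apply to it. The concern is confined to the continuous secondary scales that do not measure symptoms.
- **Likelihood.** A reader might infer that the rule would usually pass a UP that does nothing. That needs a CBT effect below about .10 (.06 with SD 1), and nothing in the protocol shows effects that small. The Background reports medium-to-large UP effects on affect, quality of life and adjustment. Those come from small studies and are not CBT-versus-placebo effects, but they make near-zero responsiveness less plausible for PANAS, QLI and MI than for personality traits.
- **Wording of the rule.** Analyses describes the margin as 50% of the CBT effect and does not repeat .30, so it could be read as outcome-specific. However, Sample size ties the margin to the pooled estimate precisely because outcome-specific effects are lacking, so no other margin is available.
- **Intent.** No sentence promises a non-inferiority verdict on each secondary scale, and a full analysis plan might settle this. The text points the other way, though. The rule names no outcomes, the post-hoc power analysis in the same paragraph is limited to the primary ones, and satisfaction, a secondary outcome, is given a non-inferiority margin.
- **Transparency.** Within-group effect sizes will be reported and would show a scale that neither arm moves. This helps a careful reader, but it does not make the non-inferiority statement informative.

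**Conclusion.** The point holds in a limited form. On a fair reading, the .30 margin governs the continuous secondary scales, and the protocol does not show the CBT effect of about .60 that its own 50% logic needs on PANAS, ACQ-R, NEO-FFI, QLI or MI. The support is weakest for the NEO-FFI traits.

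Wherever the CBT effect is .30 or less, a pass shows no preserved benefit. How often a UP without effect would pass depends on that unknown effect. On the plan's inputs it ranges from 80% at zero to 5% at .30, and it is below 1% from .40 upwards. With SD 1 it is 66% at zero. These figures assume independent observations, a one-sided 5% test and 95 analysed per arm.

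The point does not touch the BDI-II and BAI conclusions or the sample size, and it does not say whether .30 is right for the symptom outcomes.

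**What to change.** In Sample size and Analyses, state that the .30 non-inferiority rule applies to BDI-II and BAI, with ODSIS and OASIS as supportive symptom measures. For NEO-FFI, report the UP–TAU difference with its confidence interval and make no non-inferiority claim. Do the same for PANAS, ACQ-R, QLI and MI, unless a CBT-versus-placebo effect on the scale concerned is cited to justify a margin. The separate satisfaction margin is outside this change.

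The cost is a sentence or two in each section, with no new data and no change to recruitment. The trial gives up some formal non-inferiority statements on secondary scales and reports estimates there instead.
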